### Study design

2.1

The study uses a single-group, prospective pre-post mixed-methods design to assess the acceptability and feasibility and to estimate effect sizes of the newly developed NBHM intervention on the primary outcome of QOL and secondary outcomes of grief processing (intensity/severity of grief symptoms, directed attention and psychological symptoms). The mixed-method approach will yield important information from both survey and qualitative data regarding the acceptability and feasibility of the NBHM intervention. No comparator is used given the study’s primary aim is to evaluate the feasibility of the new intervention (Figure 2).

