#### Quality of life

2.6.5

QOL domains, including physical, social and psychological functioning and health perceptions, will be measured using the PROMIS-29 (60, 61) at all three time points. The PROMIS is a collection of short-form profile instruments (social, psychological, and physical function, pain, fatigue, sleep disturbance, health satisfaction) (62).

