#### Power

2.7.1

Consistent with the analytic model (linear mixed-effect model, LMM) for estimating the change in the primary endpoint, QOL, a simulation-based approach (63) to estimate power to detect effect sizes (ESs) ranging from 0.2 (small) to 0.4 (moderate) is used. Because there is no existing literature on the within-participant correlation (
ρ
) of the outcome over time, three scenarios for 
ρ
(0.3, 0.4, 0.5) are used with 1,000 simulations for each of the three ESs (0.2, 0.3, 0.4) and the baseline sample sizes ranging from 40 to 70 for each simulation. For the power of 0.80 and *α* = 0.05, an initial sample size of 42 FCGs is adequate to detect an ES of 0.4 if 
ρ=
0.4 and 55 FCGs are needed if 
ρ=
0.3; 51 FCGs will be adequate to detect an ES of 0.3 if 
ρ=
0.5 and 65 FCGs are needed if 
ρ=
0.4; and more than 70 FCGs will be needed to detect an ES of 0.2 across all scenarios for 
ρ.
 To be conservative and within the budget, and assuming a 20% attrition rate by week 12, a total of 70 FCGs will be recruited.

Basic summary statistics for demographic characteristics and co-morbid conditions in FCG will be calculated. Because the study involves repeated measurements on the same FCG, basic summary statistics will be generated for each of the three time points. All analytic procedures envisioned for this exploratory project are consistent with general best practices, including recommendations made by the National Research Council panel on the prevention and treatment of missing data in clinical trials (64).

Any technology issues that emerge will be meticulously monitored and tracked. To estimate the change in FCGs’ outcomes across time, an LMM for continuous outcomes will be used. The results will be presented in both the original and standardized scales with estimated confidence intervals and no statistical hypothesis testing will be performed. The random effects will account for the correlation/covariance within the FCGs arising from the repeated measurements on each FCG. Further exploratory analyses will be conducted to assess the potential heterogeneity of the longitudinal profile of the outcomes by FCGs’ baseline characteristics (baseline QOL, age, gender, and relationship). Operationally, this heterogeneity will be assessed through interactions between time and any of the FCGs’ baseline characteristics. Estimates from these analyses will provide directional effects for a later larger-scale study.

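### With QOL as the outcome, the time-by-baseline-QOL interaction has the Time 1 score in both response and moderator, so regression to the mean alone would make the worst-off caregivers appear to improve most

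*Protocol article*

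**What the plan says.** All references are to the Protocol article.

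- **Outcome.** Section 2.1 plans effect-size estimates "on the primary outcome of QOL and secondary outcomes of grief processing". Section 2.6.5 says that the QOL domains "will be measured using the PROMIS-29 (60, 61) at all three time points".
- **Model.** Section 2.7.1 states: "To estimate the change in FCGs’ outcomes across time, an LMM for continuous outcomes will be used". Random effects handle the correlation between a caregiver's repeated measurements. Results are reported as estimates with confidence intervals, without hypothesis tests.
- **Heterogeneity.** The same section lists the moderators as "baseline characteristics (baseline QOL, age, gender, and relationship" and fixes the method: "this heterogeneity will be assessed through interactions between time and any of the FCGs’ baseline characteristics".
- **Use.** It then says: "Estimates from these analyses will provide directional effects for a later larger-scale study".
- **Design.** Section 2.1: "The study uses a single-group, prospective pre-post mixed-methods design". There is no comparator.

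The article does not say how the Time 1 QOL score is handled when QOL is itself the outcome, and it does not mention regression to the mean.

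**The concern.** In a single group, an LMM can estimate change from baseline only if the Time 1 score is among the responses. When baseline QOL is then interacted with time for the QOL outcome, the same number sits on both sides of the model. The interaction becomes the regression of (follow-up minus baseline) on baseline. A caregiver whose Time 1 score is low partly through measurement error or a bad week will tend to score higher later, whatever the intervention does.

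The sign of this one interaction is therefore largely settled before any data are collected. The plan intends to pass the estimate on as a direction for later work. A control arm would show the same regression to the mean and so reveal it, but this design has none. Section 4 (Limitations) mentions the missing control group only as a limit on generalizability.

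**Working it through.** The plan gives no figure for this interaction, so there is none to reproduce. The check derives the value expected when there is no heterogeneity and compares it with simulation.

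**Inputs from section 2.7.1.** rho = 0.3, 0.4, 0.5; effect sizes 0.2 to 0.4; 70 recruited; 20% attrition by week 12, leaving 70 × 0.8 = 56.

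**Assumptions.** Every caregiver has the same true change; the variance σ² is equal across visits; rho is below 1 because of measurement error or transient fluctuation.

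**Step 1: expected interaction.** Let Y1 and Y3 be QOL at Time 1 and Time 3.

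Cov(Y3 − Y1, Y1) / Var(Y1) = (rho·σ² − σ²) / σ² = rho − 1 = −(1 − rho)

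| rho | Expected interaction (SD per SD of baseline) |
|---|---|
| 0.3 | −0.7 |
| 0.4 | −0.6 |
| 0.5 | −0.5 |

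A caregiver 1 SD below the mean at baseline would thus appear to gain 0.5 to 0.7 SD more than an average caregiver, with no true difference. The largest mean change considered in the power section is 0.4 SD.

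**Step 2: simulation with no heterogeneity.** Everyone receives the same shift of +0.3 SD, N = 70, 20% lost at week 12. Two versions were run: a random-intercept LMM with time × baseline QOL and Time 1 in the response (200 runs per rho), and a regression of week-12 change on baseline (3,000 runs per rho).

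| rho | LMM: mean interaction | LMM: 95% CI excludes 0 | Regression: mean slope | Regression: 95% CI excludes 0 |
|---|---|---|---|---|
| 0.3 | −0.72 | 100% | −0.70 | 99.8% |
| 0.4 | −0.60 | 100% | −0.60 | 99.5% |
| 0.5 | −0.51 | 99% | −0.50 | 98.0% |

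**Step 3: is the shared score the cause?** In the same data:

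- With age as the moderator, the LMM interaction averages about 0.00 and the interval excludes zero in 3.5% to 4.5% of runs.
- With baseline QOL as the moderator but only Times 2 and 3 in the response, it averages −0.01 to 0.00 and the interval excludes zero in 5.5% to 6.5% of runs.

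The artefact appears only when Time 1 QOL is on both sides.

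**Step 4: higher rho.** These values are assumed and lie outside the plan's range (regression version).

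| rho | Mean slope | 95% CI excludes 0 |
|---|---|---|
| 0.7 | −0.30 | 85% |
| 0.8 | −0.20 | 67% |
| 0.9 | −0.10 | 39% |

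The artefact shrinks as rho rises but keeps its direction.

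**Step 5: the alternative.** For change against the mean of the two scores, the numerator is Cov(Y3 − Y1, (Y1 + Y3)/2) = (Var(Y3) − Var(Y1)) / 2. With equal variances this is 0, so the built-in slope disappears.

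**The case against.** **The analysis is exploratory and nothing is tested.** Correct, and it limits the severity. A reader might take the exclusion rates above as the false-positive rate of a planned test. The documents do not support that, because section 2.7.1 rules out hypothesis testing. The rates only describe how consistently the reported interval would point the wrong way. The bias lies in the estimate and interval, which are what the plan reports and carries forward.

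**The model equation is not given.** Also correct. The moderators apply to several outcomes, and for grief and directed attention baseline QOL shares no score with the response. If only Times 2 and 3 were modelled, the artefact would vanish (Step 3). But that model would describe the profile between weeks 6 and 12, not change from baseline. An LMM for change over three time points, with a time interaction, most naturally includes Time 1. The point remains conditional on that reading.

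**The size depends on rho.** It does. The plan chose 0.3 to 0.5 as scenarios because it found no published values, so the true figure could be smaller. If some of the low correlation reflects real differences in change between caregivers, not all of 1 − rho is artefact.

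**The harm is conjectural.** In part. A reader might infer that the later study will be aimed at caregivers with low QOL; the article says no such thing. It speaks only of directional effects, and section 5 anticipates a randomized trial, in which moderation could be examined against a control. What stands is that the direction handed to that trial would be uninformative.

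**Conclusion.** The point holds for one exploratory interaction: baseline QOL by time, with QOL as the outcome and Time 1 in the response. Under a common true change and equal variances, its expected value is −0.7 to −0.5 SD per SD of baseline across the plan's rho range, and about −0.2 at an assumed rho of 0.8. Within the plan's range, the interval would nearly always suggest that those with the lowest baseline QOL benefit most.

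A reader might infer that the study's QOL result is itself invalid. The documents do not support that. The estimate of mean change, the feasibility and acceptability aim, and the age, gender and relationship interactions do not carry this coupling. The anxiety and depression scores come from the same PROMIS-29 (section 2.6.6), so baseline QOL calls for caution as their moderator too. The wording should be fixed, but no main conclusion of the study depends on it.

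**What to change.** In section 2.7.1:

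1. Drop baseline QOL as a time-moderator when QOL is the outcome. Keep it for grief and directed attention, and interpret it with caution for anxiety and depression.
2. If dependence on initial level is still of interest, relate change to the mean of baseline and follow-up QOL (Oldham's method). Beside any estimate based on baseline, report the slope −(1 − rho) expected from regression to the mean, using the observed rho.
3. State that neither result will serve as a directional effect for the later study.

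Blomqvist's correction is not a ready substitute, because it needs a measurement-error variance that the documents do not give.

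The cost is a sentence or two of analysis text, with no change to data collection or sample size. The caption of Figure 1 does not list baseline QOL among the potential moderators, so the conceptual model loses nothing. The downside is that one exploratory interaction is lost or replaced. Oldham's method has assumptions of its own, and a single arm still cannot fully separate true dependence on initial level from regression to the mean.

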The provision of low-cost self-care resources that address bereaved FCGs’ QOL and emotional health post-patient death from cancer is both a critical need and a research gap (6, 10). The present study is novel because it assesses a newly developed nature-based healing meditation (NBHM) intervention that blends meditative practices with nature imagery in an on-line format to promote individualized grief processing among bereaved cancer FCGs. Importantly, on-line delivery of psychotherapeutic interventions have grown with demonstrated efficacy in the past two decades (47). There is growing research that has tested both meditative practices and nature interventions via virtual and online formats (36, 48–51) demonstrating an evidence-base that is complementary given interrelated components such as the ‘meditative qualities and reflection opportunity’ often associated with nature. Thus, combining meditation with exposure to nature as an integrated intervention is posited to yield superior benefits to either alone (52). The six-week technology-mediated intervention described in more detail in the methods section offers auditory guided nature-meditation modules that are anchored in six different natural settings (spring meadow, fall meadow, wooded forest, beach scene, solar system/night sky, evening sky), from which participants may select. Importantly, integration of grief adaptation theory, mechanisms underlying meditative practices that promote mindful awareness, and attention restoration theory provides a conceptual avenue for producing an intervention able to support bereaved FCGs.

The purpose of this paper is to describe the research protocol for assessment of a newly developed nature-based meditation intervention for bereaved FCGs of patients who died from cancer. The research aims include: (1) evaluate the acceptability and feasibility of the content and delivery of the NBHM intervention for use by bereaved cancer FCGs; and (2) assess the potential of the NBHM intervention towards improving parameters of bereavement recovery (see Figure 1).

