### Intervention

2.4

Six modules integrating meditative practices with nature imagery were developed for online delivery, drawing on the strength of our team’s previous meditation and nature intervention work (54, 55), with input from a meditation therapist professional. Each module is framed and anchored to the same core constructs: attention restoration, grief awareness and processing, psychological wellbeing and promotion of QOL. Once the content was developed, each 15-to-20-min module was audio-recorded by the technical team with the verbiage delivered by an experienced meditation provider. A brief version (~10 min) of the same content was also recorded using a simulated voice for those with less time to commit to the practices or who might prefer an alternative voice. After the modules were recorded with both voice versions, all were alpha tested by research team members to identify overall functionality and to identify any problems needing addressment prior to use with actual bereaved CGs. All modules will be available to the enrolled CGs via a private online link through Qualtrics. The study project manager will send each participant the access link to all modules once baseline data is collected. The intervention modules include orientation to the content, clear guided instruction, and motivational content to support the establishment of a regular practice. The meditations are all designed to be done seated comfortably in a chair. Participants will be encouraged to wear headphones and eye masks to focus on the auditory experience.

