### Fidelity

2.5

Standard NIH recommendations (dose, training, delivery, receipt, enactment) for socio-behavioral research will be used for intervention fidelity (56) and are depicted as following. Participants are asked to commit to completing a minimum of 4 modules over the 6-week period. The privately accessible website will record when an FCG accesses any module and the duration of use to establish doses received by individual participants. Because the intervention modules are pre-recorded and all training content on the web is uniform, there is no deviation in the provision of the intervention across participants. The intervention site which is accessible to study participants, records access and time spent with modules. Weekly emails, texts or calls (based on preference), using a toll-free access number during weeks 1–6, will provide reminders to engage with the nature meditations and to query if any technology assistance is needed. At week 12, meditation module access during the follow-up phase between weeks 7 to 12 will be monitored to assess sustained use of the intervention. All study staff will receive standardized training with active feedback prior to engaging with study participants. Additionally, their training will equip them to be available to provide technical troubleshooting assistance for participants.

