Acceptability will be assessed at two levels: (1) among FCGs approached, how many consent to participate; and (2) among participants, how many complete the intervention. For feasibility we establish the following minimum parameters: FCGs must complete a minimum 4 modules during the 6-week period. The study will use latent class analysis to group FCGs into several clusters based on AIM and FIM measures and examine whether FCGs’ demographic and outcome measures differ by cluster. This analysis will inform the relationship between acceptability and feasibility and the outcomes. The web-tracking data will be used to examine the time of day and duration each FCG uses each module. An exploratory analysis of the association between timing and duration of use and endpoints will be performed to estimate a response curve and identify the minimum intervention use associated with meaningful improvement and the potential intervention saturation point (i.e., the effect plateaued).

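### A minimum use and a saturation point cannot be identified from self-selected use in one uncontrolled group with about 56 week-12 completers

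*Protocol article*

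**What the plan says.** Section 2.7.1 (Power, which also holds the analysis text) announces: "An exploratory analysis of the association between timing and duration of use and endpoints will be performed to estimate a response curve". The stated purpose is to "identify the minimum intervention use associated with meaningful improvement and the potential intervention saturation point", the latter explained as the place where the effect levels off.

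The rest of the article fixes the setting for that analysis:

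- **Design.** Section 2.1 describes a "single-group, prospective pre-post mixed-methods design" and states that there is no comparator.
- **Exposure.** Section 2.5 (Fidelity) says the website "will record when an FCG accesses any module and the duration of use to establish doses received by individual participants". It asks for at least four modules in six weeks. Use beyond that is left to the participant, and the Introduction describes six natural settings "from which participants may select".
- **Versions.** Section 2.4 (Intervention) gives a standard recording of 15 to 20 minutes per module. It adds: "A brief version (~10 min) of the same content was also recorded using a simulated voice". The brief version is meant for people who are short of time or would like a different voice.
- **Numbers.** Section 2.7.1 plans on "assuming a 20% attrition rate by week 12, a total of 70 FCGs will be recruited". It considers effect sizes of 0.2, 0.3 and 0.4 and within-participant correlations (rho) of 0.3, 0.4 and 0.5.

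**The concern.** Both target quantities need the outcome at a given level of use to be attributable to that use. Nothing in the design provides this.

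The participant chooses the amount of use. It may follow baseline distress, free time or early benefit, and each of these can affect the outcome by itself. The Introduction also says that grief normally eases over time, so with no comparator a meaningful improvement at some level of use could appear with an inert recording.

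The unit of use matters too. Minutes mean different things in the two versions, and version choice is tied to available time, which may itself relate to outcome.

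The study is meant to refine the intervention before a randomised trial (Conclusion). A minimum or plateau reported from this curve could be taken up there although it reflects who chose to use the modules. The article does not say that this will happen, but it gives no caution against it.

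**Working it through.** **1. Number available.** 70 × (1 − 0.20) = 56 with week-12 data, from the article's own figures. Week-6 data could come from up to 70 people.

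**2. Precision of a contrast between use levels.** Split the sample into equal use groups of size m. With equal variances over time and effects in baseline-SD units (an assumption, since the article does not name the standardiser), the SD of a change score is √(2(1 − rho)). The 95% half-width for a difference in mean change between two of these groups is

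1.96 × √(2(1 − rho)) × √(2/m).

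For n = 56 and two groups, m = 28 and √(2/28) = 0.267:

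- rho = 0.5: 1.96 × 1.000 × 0.267 = 0.52
- rho = 0.3: 1.96 × 1.183 × 0.267 = 0.62

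| n | use groups | half-width (SD), rho 0.5 to 0.3 |
|---|---|---|
| 56 | 2 | 0.52 to 0.62 |
| 56 | 3 | 0.64 to 0.76 |
| 56 | 4 | 0.74 to 0.88 |
| 70 | 2 | 0.47 to 0.55 |

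Every entry exceeds 0.4, the largest whole-sample effect considered.

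Adjusting for baseline instead of using change replaces √(2(1 − rho)) by √(1 − rho²), which is 0.866 at rho 0.5 and 0.954 at rho 0.3. With two groups of 28 the half-width is then 1.96 × 0.866 × 0.267 = 0.45 to 1.96 × 0.954 × 0.267 = 0.50. This is better, but still wider than 0.4.

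**3. Locating a plateau.** The article gives no distribution of use, so this step is illustrative. Assume log-normal use with a median of 8 sessions and a log-SD of 0.6, and a true effect that rises linearly to 0.3 or 0.4 SD at 8 sessions and is flat afterwards. A linear-plateau model was fitted in 1,000 simulated studies per setting, with n = 56 and rho 0.3 or 0.5. The 5th to 95th percentiles of the estimated plateau ran from 2.5 to 24 sessions, where 24 is the upper limit of the search. The fitted slope had the wrong sign in 26% to 34% of runs. Results with n = 70 were nearly the same.

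**4. Selection alone, with no effect of use.** Suppose use is related to baseline QOL and has no other link to follow-up, and that unadjusted change is analysed. Then

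corr(use, change) = corr(use, baseline) × [−√((1 − rho)/2)].

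The bracket is −0.59, −0.55 and −0.50 at rho 0.3, 0.4 and 0.5.

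- If corr(use, baseline) = −0.3: +0.18, +0.16, +0.15
- If corr(use, baseline) = −0.1: +0.06, +0.05, +0.05
- If more distressed caregivers use the modules less, the sign reverses.

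The article supports no particular value. The result shows that regression to the mean can make a spurious association in either direction, and that adjusting for baseline removes this component.

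**5. Minutes against content.** Four modules take 4 × 10 = 40 minutes in the brief version and 4 × 15 = 60 to 4 × 20 = 80 in the standard one, a ratio of 1.5 to 2. Sixty minutes is six brief modules, or three to four standard ones.

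**The case against.** The article is cautious in several respects. It calls the analysis exploratory, speaks of association, qualifies the saturation point as potential and rules out hypothesis testing. The curve is not part of either research aim, and the Limitations section admits self-selection and the missing control group. All of this stands, and it limits the severity. It does not rescue the aim: calling the work exploratory does not make a threshold or plateau attributable to use, and the Limitations section does not apply its caveats to this curve.

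Four stronger readings are tempting, and the documents do not support them.

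- **The fidelity claim is contradicted by the two versions.** A reader might infer this from the sentence that "there is no deviation in the provision of the intervention across participants". That sentence concerns the provision of uniform pre-recorded material, and every participant receives the link to all modules. Different choices among them are uptake, which the same section records separately. There is no contradiction.
- **Minutes will be pooled across versions.** The article never says so. It also tracks module access (Section 2.5) and the number of times and weeks of use (Section 2.6.2), and its requested minimum is a module count. What stands is that the curve is described in terms of duration, and duration has no common meaning across versions.
- **The analysis will be unadjusted.** The article names no adjustment for this curve, but a condensed article may leave that to the analysis plan. The silence is not itself an error.
- **A curve with two change points cannot be estimated.** The plan specifies no such model. A minimum use could simply be where a smooth curve crosses a threshold. The supportable statement is that the estimates would be too imprecise to use.

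**Conclusion.** The concern holds as a limited one. The article sets itself the task of identifying two quantities that a single uncontrolled group with self-selected use cannot attribute to use. It also could not locate them precisely: half-widths of about 0.52 to 0.62 SD for the simplest two-group contrast at n = 56, against effects of 0.2 to 0.4 SD.

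That calculation rests on the article's own sample size, attrition and correlations, on equal use groups and on equal variances over time. The plateau simulation rests on an assumed distribution of use, and the regression-to-the-mean figures on an assumed correlation, so both are illustrations only. The difference in minutes between versions follows directly from the stated module lengths.

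A reader might infer that the plan makes a causal or confirmatory dose claim. It does not. The overreach lies in undertaking to identify a minimum and a plateau. It does not affect the feasibility aim or the main estimates of change, but it should be corrected.

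**What to change.** In Section 2.7.1, replace the undertaking to identify a minimum use and a saturation point with a descriptive, hypothesis-generating use-outcome association reported with 95% confidence intervals. State that it will not be used to set required use in the next trial.

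For the analysis itself:

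- Model the follow-up outcome on use in weeks 1 to 6, adjusted for baseline outcome and months since death. Both are already collected.
- Measure use as modules completed, or as the fraction of module length played. Record the version, and adjust for it where the logs allow.
- A smooth curve may be shown with its interval; there is no need to force a straight line.

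Adjustment will reduce, not remove, the influence of why people used the modules, and it cannot stand in for a comparator. The text should say so.

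The cost is a change of wording, a few covariates and one variable derived from the web logs, provided that the logs distinguish versions, which the article does not state. The downside is the loss of an exploratory claim.
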